**Insulin group**

In the Insulin group both soluble insulin and premixed insulin will be prescribed. There will be no brand restriction. Both premixed insulin and soluble insulin will be administered subcutaneously in the deltoid region. Total daily dose of premixed insulin at initiation will be calculated for most patients as 0.3 IU/kg body weight. However for patients admitted with high blood glucose levels they will be managed on sliding scale with soluble insulin their starting dose will be based on total daily requirement. The total daily dose will then be divided into two: two-thirds of the dose will be administered in the morning 30 minutes before breakfast and one-third of the daily dose will be administered in the evening 30 minutes before supper. The total dose of insulin will be titrated for each patient to achieve the above glycemic targets. Patients who may not achieve glycemic targets on their out-patient doses after attempts at titrations will be admitted to the ward and treated with soluble insulin to determine their new optimum insulin requirements. All patients will be educated by both nurses and doctors while on admission on the disease and self-administration of the correct doses of insulin before discharge.

**Treatment failures**

Supplemental insulin for treatment failures in the Metformin group will be prescribed according to the same protocols in the insulin group.

DATA COLLECTION

Basic demographic data will be recorded. They will be followed through their index pregnancy, with 2-weekly blood glucose checks in hospital. All laboratory samples will be collected and analyzed at the diabetes research laboratory by staff of the same laboratory. Venous blood will be used for blood glucose profile analysis. Analysis of Fasting Blood Glucose (FBG), one- hour post-prandial glucose (1HPG), two- hour post-prandial glucose (2HPG) will be done using the Mindray BS-400^®^ (Mindray Medical Int. Ltd, China) chemistry analyzer. The method for glucose determination will be enzymatic photometric testing. Urinalysis, weight records (using Seca^®^(gmbh&Co. Kg Germany)) and cost of treatment will also be documented. The optimal dose of metformin required for optimal glycaemic control will be recorded for each patient. Peri-partum events like gestational age at delivery, type of delivery, fetal birth weight, and NICU admissions will be retrieved from patient notes.

STATISTICAL ANALYSIS

In analyzing the data, summary statistics will include appropriate tables and charts. Categorical data will be represented by pie and bar graphs and continuous data with histograms.

For inferential statistics, significant difference of mean observations using one-tail student’s t-test and z-score for differences in proportions where applicable. The differences in trends of glycaemic profile over time between the study groups will be assessed by two-way repeated measures analysis of variance (ANOVA).

Significance level (p-value) will be set at α = 0.05. Data analysis will be done using statistical package for social science **(SPSS** version 20).

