**HYPOTHESES**

- The glycaemic control will be equally effective with metformin therapy compared to insulin in pregnant diabetics in Ghana.
- Weight gain in mother and baby will be significantly lower on metformin therapy compared to insulin.

*Rationale:* Metformin has been shown to be equally effective and safe as insulin in the management of GDM. Poor compliance to insulin due to high cost, accessibility, storage difficulties and the discomfort of repeated injections is expected to make metformin a more suitable choice.

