**PHARMACODYNAMICS**

Metformin is an effective oral hypoglycemic agent that improves insulin sensitivity. ^25^ Metformin has a greater postprandial effect than the sulfonylureas and insulin, and is therefore more useful in patients with postprandial hyperglycaemia. The sulfonylureas and insulin on the other hand are more effective in managing poorly controlled fasting hyperglycaemia. ^15^
 Metformin reduces free testosterone levels and increased sex hormone-binding globulin (SHBG). It improves menstrual irregularities leading to spontaneous ovulation and improved ovarian response to conventional ovulation induction therapies. ^25,^

The introduction of metformin for the treatment of polycystic ovary syndrome (PCOS) provided evidence supporting its use in pregnant women. ^28^ Metformin has been recommended for use during pregnancy for the treatment of gestational as well as preexisting diabetes mellitus. ^29^

The exact mechanism of action of Metformin is not fully understood despite its wide clinical usage. Metformin does not stimulate insulin secretion.
It exerts its hypoglycaemic effect via metabolic activities at several sites of action, including liver, adipocytes, intestine, and muscle cells. The activities in these sites of action (Biophases) include:

1) Decreased hepatic glucose output due to decreased hepatic gluconeogenesis and increased glycogenesis and lipogenesis; ^30^

2) Reduced rate of intestinal glucose absorption; ^31^ and

3) Increased glucose uptake by muscle cells and adipocytes ^32^

The relative contribution of these individual sites of action to the overall glucose-lowering effect is unknown and a subject of continuing research in animal models^33^. This is because the dose-response relationship of the metabolic effects in individual organs and tissues is obscured by the multifactorial mechanism of metformin and the complex nature of glucose homeostasis in-vivo ^33^

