**EXPECTED OUTCOME**

It is expected that pregnant diabetics treated with metformin will have a lower 2HPG levels at the end of the study than those treated with insulin. The primary outcome is the difference in the 2HPG level between the metformin and insulin group. The rationale for selecting 2HPG is that by its mechanism of action, metformin is expected to have a more significant blood glucose lowering effect in the postprandial period than the fasting period. Hyperglycaemia in the prandial period is related to insufficient suppression of hepatic glucose output, poor insulin release and ineffective glucose disposal in target tissues (especially muscles) by insulin (insulin resistance) and metformin affect all these Biophases.^30-32^

Secondary outcomes to be measured include glycaemic profile (measured by FBG, 1HPG, and HB1AC), fetal birth weight, maternal weight gain and caesarean section rate which are expected to be lower in the metformin group, number of NICU admission which is expected to be higher in the insulin group. If found to be effective it may form the basis for developing a policy for Diabetes Mellitus care in pregnancy at primary and secondary level of healthcare instead of the current tertiary level of care.

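### Means are compared with a one-tailed t-test at an unreduced 0.05; read with the stated expectations, this doubles the error in metformin's favour and leaves no rejection region for higher values on metformin.

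*Protocol*

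**What the plan says.** Protocol, Statistical Analysis, gives the test for means: "For inferential statistics, significant difference of mean observations using one-tail" Student's t-test, followed in the same sentence by a z-score for proportions. The level follows: "Significance level (p-value) will be set at α = 0.05". No reason for one tail is given, the direction of the tail is not named, and α is not reduced. The same section assigns the trends of glycaemic profile over time to a two-way repeated-measures ANOVA.

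The direction has to be taken from elsewhere. Expected Outcome states: "It is expected that pregnant diabetics treated with metformin will have a lower 2HPG levels at the end of the study", and "The primary outcome is the difference in the 2HPG level between the metformin and insulin group". For secondary outcomes it lists "fetal birth weight, maternal weight gain and caesarean section rate which are expected to be lower in the metformin group". The second item under Hypotheses also predicts lower weight gain in mother and baby on metformin.

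Two other places point away from a one-directional question. The first item under Hypotheses is "The glycaemic control will be equally effective with metformin therapy compared to insulin in pregnant diabetics in Ghana". Pharmacodynamics says: "The sulfonylureas and insulin on the other hand are more effective in managing poorly controlled fasting hyperglycaemia".

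Sample Size Determination gives 47 per group (52 after a 10% allowance), a difference of 0.22 mmol/L in mean 2HPG, 80% power and α = 0.05. It states neither the sidedness nor the SD.

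**The concern.** A one-tailed test at the full 0.05 is defensible only if a result in the other direction is impossible or of no interest. Neither holds here. The protocol's own pharmacology gives a reason why fasting glucose might be worse on metformin, and its first hypothesis is equality, not superiority. The Problem Statement says that metformin's use in pregnancy has been held back by a lack of efficacy and safety data. Expected Outcome says that a favourable result may support a policy moving care to the primary and secondary levels. Such a decision needs an analysis that can also show higher glucose or greater weight gain on metformin.

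Two things are at stake. A chance finding in metformin's favour passes at twice the rate that readers normally assume. A substantial difference against metformin in a mean would be reported only as not significant.

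**Working it through.** **Inputs.** Difference 0.22 mmol/L, n = 47 per group, power 80%, α = 0.05 (Sample Size Determination); one-tailed t-test at 0.05 (Statistical Analysis); direction lower on metformin (inferred from Hypotheses and Expected Outcome). The SD is not stated.

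**1. Error rate.** With no true difference, the chance of falsely declaring metformin better is 0.05 for the one-tailed test and 0.05/2 = 0.025 for a two-sided 0.05 test. A one-tailed 0.05 test uses the same cut-off as a two-sided test at 0.10. With 2 × 47 − 2 = 92 degrees of freedom, the critical t falls from 1.986 to 1.662.

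**2. The opposite direction.** As an illustration, take a result 2.5 standard errors against metformin. The one-tailed p is Φ(2.5) = 0.994. The two-sided p is 2 × (1 − 0.994) = 0.012 (0.014 from the t distribution).

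**3. The plan's figure of 47.** It cannot be reproduced without the SD. Solving n = 2(z_α + z_β)²·SD²/δ² for the SD, so that SD = δ·√(n/2)/(z_α + z_β), gives:

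- If sized one-tailed: 0.22 × √23.5/(1.645 + 0.842) = 1.066/2.486 = 0.43 mmol/L.
- If sized two-sided: 0.22 × √23.5/(1.960 + 0.842) = 1.066/2.802 = 0.38 mmol/L.

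Both SDs are back-calculated assumptions. Nothing in the protocol chooses between them.

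**4. Cost of a two-sided test, if 47 was sized one-tailed (SD 0.429).**

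- 47 per group: SE = 0.429 × √(2/47) = 0.0885; 0.22/0.0885 = 2.486; power = Φ(2.486 − 1.960) = 0.70 (non-central t: 0.698).
- 52 per group: SE = 0.429 × √(2/52) = 0.0841; 0.22/0.0841 = 2.615; power = Φ(2.615 − 1.960) = 0.74 (non-central t: 0.742).
- Difference detectable with 80% power at 47 per group: 0.22 × 2.802/2.486 = 0.25 mmol/L.
- n for 80% power at 0.22 mmol/L: 47 × (2.802/2.486)² = 59.7, so 60 per group before dropout.

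**5. Cost if 47 was sized two-sided (SD 0.381).** Power at 47 per group stays at 80%. The one-tailed test now planned would have Φ(2.802 − 1.645) = 0.88.

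**6. What the two-sided test gains.** If metformin truly raised 2HPG by 0.22 mmol/L (assumed SD 0.43, 47 per group), the two-sided test would show this with about 70% power. The one-tailed test has no region in which it could.

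**The case against.** Several objections narrow the point.

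- **Total error is controlled.** The one-tailed test has a type I error of 5%, as a two-sided 0.05 test does. Only the error in one direction doubles, relative to convention. A reader might infer that the overall false-positive rate doubles; it does not.
- **The tail is inferred.** Statistical Analysis names no direction. For 2HPG and for weight gain in mother and baby the inference is firm. For FBG, 1HPG and HbA1c it depends on whether the clause about lower values in Expected Outcome reaches back to the glycaemic profile.
- **Not every analysis is one-directional.** A reader might infer that the trial cannot show metformin to be worse for mother or baby at all. The protocol does not support that. The repeated-measures ANOVA of glucose trends has a non-directional F test, so a worse glucose course on metformin could appear there. Caesarean section and NICU admission are proportions; NICU is a "number of NICU admission which is expected to be higher in the insulin group", but whether the single tail also governs the z-test is unclear. For birth weight, abnormally low values on metformin would lie inside the inferred rejection region, so only heavier babies are out of its reach.
- **The direction was set in advance**, with a mechanistic rationale for 2HPG, so this is not a tail chosen after seeing data. That is fair, but a prior expectation does not make the opposite result uninteresting.
- **A two-sided superiority test would not establish equal effectiveness either.** This is correct: equality needs a margin, and none is given. It does not defend the one-tailed test, which fits that hypothesis no better.

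What remains is the t-test itself. The ANOVA addresses trends over time; it does not replace the comparison of mean 2HPG on which the study is sized, and it does not cover maternal weight gain or birth weight.

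**Conclusion.** The point holds for the t-tests. An unjustified one-tailed test at an unreduced 0.05 governs the primary outcome and the other comparisons of means. With the tail as inferred, the false-positive rate in metformin's favour is 5% instead of 2.5%. The tests on 2HPG, the other glucose means, maternal weight gain and birth weight have no rejection region for higher values on metformin. This sits badly with a hypothesis of equal control and with the protocol's own statement about fasting hyperglycaemia.

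The error-rate result needs no assumption beyond the direction of the tail. The power consequence is conditional: it ranges from no loss (47 sized two-sided, SD about 0.38 mmol/L) to a fall from 80% to about 70% at 47 per group (sized one-tailed, SD about 0.43 mmol/L). A demonstrated loss of power cannot be claimed, because neither the sidedness nor the SD behind 47 is stated.

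**What to change.** In Statistical Analysis, replace the one-tailed t-test by a sentence such as: *Between-group differences in means and proportions will be tested two-sided at a significance level of 0.05 and reported with 95% confidence intervals.* This also settles the sidedness of the z-test. A one-sided test at 0.025 is appropriate only if a non-inferiority claim with a stated margin is adopted; it corresponds to the same 95% interval.

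In Sample Size Determination, state the sidedness, the SD and its source, and the resulting two-sided power.

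The change needs no new data and should be made before results are compared by group. If 47 was sized one-tailed, the stated power for 0.22 mmol/L becomes about 70% at 47 per group (74% at 52) and the difference detectable with 80% power at 47 per group rises to about 0.25 mmol/L; keeping 80% power at 0.22 mmol/L would take 60 per group before dropout. If it was sized two-sided, there is no cost.

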**Eligibility criteria**

Eligible subjects will be women aged 18 to 45 years who are pregnant with single fetus at gestational age of 20 to 30 weeks and have been diagnosed with type 2 DM or Gestational Diabetes and met the Hospital’s criteria for starting insulin therapy. The criteria for the diagnosis of GDM and DM will be a plasma glucose concentration of greater than or equal to 7 mmol/L after an overnight fast or plasma glucose concentration of equal to or greater than 11.1 mmol/L 2 hours after a 75g glucose drink.^1^

The current criteria for starting insulin therapy in patient with GDM at the diabetes clinic of KBTH are at least one following:

- FBS > 5.1 mmol/l
- 1HPG > 10.0 mmol/L or
- 2HPG > 8.5 mmol/L.

Subjects diagnosed according to the above criteria that are unable to achieve the above targets following management on diet and exercise will be eligible for the study.

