**Exclusion criteria**

Exclusion criteria will include patients with insulin dependent Diabetes Mellitus and patients with contraindications to metformin therapy.

SAMPLE SIZE DETERMINATION

Power calculation: The power calculation is based on the difference in 2HPG expected between the metformin and insulin groups at 34 weeks gestation. Using the two sampled mean formula^34^, the estimated sample size was 47 per group. From pre-trial estimates the minimum difference in mean 2HPG levels between the two groups of 4mg/dl (0. 22 mmol/l) is required to give a power of 80% to the study at a significance level of α = 0.05.We recruited 52 in each group to allow for a 10% non-respondent rate

TREATMENT PROTOCOL

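### Repeated measures ANOVA for the glycaemic trend does not fit a schedule in which the number of 2-weekly visits depends on entry week

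*Protocol*

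**What the plan says.** Four statements in the protocol bear on this point.

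- **Eligibility criteria:** women must be "pregnant with single fetus at gestational age of 20 to 30 weeks".
- **Data Collection:** "They will be followed through their index pregnancy", "with 2-weekly blood glucose checks in hospital".
- **Statistical Analysis:** the difference between groups in glycaemic trends "will be assessed by two-way repeated measures analysis of variance (ANOVA"). Means are compared separately: "significant difference of mean observations using one-tail" Student's t-test. The software is SPSS version 20.
- **Sample Size Determination:** the power calculation concerns the 2HPG difference "expected between the metformin and insulin groups at 34 weeks gestation".

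The protocol does not say whether time in the ANOVA means gestational age or time since entry. Nor does it say which visits form the time factor, or what happens to a woman who lacks one of them. Week 34 is given only as the time point of the power calculation, not as the end of the trend analysis.

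**The concern.** Classical repeated measures ANOVA works on a rectangular table with one row per woman and one filled cell per time point. A woman with an empty cell leaves the analysis. Here the table has unequal rows by design, because entry is spread over ten weeks and delivery dates differ. The analyst must either cut every woman back to a common window or drop women with short records.

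The choice of axis does not remove the problem.

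- **Visit number:** the three visits that every woman has by week 34 fall at 0, 2 and 4 weeks after entry. In the metformin group the first two of those weeks are dose build-up. A woman entering at week 20 would contribute nothing after week 24.
- **Gestational age:** the common points are weeks 30, 32 and 34. Week 30 is a pre-treatment value for a woman entering then, but comes ten weeks into treatment for one who entered at 20.

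At stake is the only method named for trends over time, which serves the first specific objective (comparison of blood glucose profiles). The analysis would lose precision. If late entrants, poor attenders or early deliverers are the ones who leave, the trend could also be biased.

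**Working it through.** **The plan's own figures.** The protocol gives no visit count and no sample size for the trend analysis, so there is nothing to reproduce for it. The 47 per group belongs to the comparison of mean 2HPG. It cannot be reproduced because no SD is stated, and it does not enter what follows.

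**Inputs.** Entry at 20 to 30 weeks (Eligibility criteria); interval of 2 weeks (Data Collection); week 34 as a reference point (Sample Size Determination). The distribution of entry weeks is not in the documents and is assumed.

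**Visits per woman by week 34, counting the entry visit.** Visits = floor((34 − entry week)/2) + 1.

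- Entry at 20: 14/2 + 1 = 8.
- Entry at 30: 4/2 + 1 = 3.

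Without the entry visit the range is 2 to 7.

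**What a window of K visits keeps.** Take equal numbers of women entering at weeks 20, 22, 24, 26, 28 and 30. They have 8, 7, 6, 5, 4 and 3 visits, 33 in total (mean 5.5). Women kept = those with at least K visits, out of 6. Measurements kept = K × women kept / 33. The last two columns give the range when entry is uniform over even weeks, whole weeks or days.

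| K | Women kept, even weeks | Measurements kept, even weeks | Women, uniform range | Measurements, uniform range |
|---|---|---|---|---|
| 3 | 6/6 = 100% | 18/33 = 55% | 100% | 55-60% |
| 4 | 5/6 = 83% | 20/33 = 61% | 80-83% | 61-64% |
| 5 | 4/6 = 67% | 20/33 = 61% | 61-67% | 60-61% |
| 6 | 3/6 = 50% | 18/33 = 55% | 41-50% | 49-55% |
| 7 | 2/6 = 33% | 14/33 = 42% | 21-33% | 29-42% |
| 8 | 1/6 = 17% | 8/33 = 24% | 1-17% | 2-24% |

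With 52 women per group, 17% is about 9.

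**Other entry patterns.** Adding early-skewed, late-skewed and 24-28-week-peaked entry, K = 3 keeps 47-64% of measurements and K = 8 keeps 1-29% of women.

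**Longer follow-up.** To an assumed week 40, with no earlier delivery, the visit counts are 11, 10, 9, 8, 7 and 6, total 51. The six visits common to all keep 6 × 6/51 = 71% of measurements under even-week entry and 75% under entry uniform over days. The loss is 25-29%.

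**Missed visits (illustration only).** The protocol gives no missed-visit rate. If visits were missed independently at 5% or 10%, the share of otherwise eligible women with five complete visits would be 0.95^5 = 0.77 or 0.90^5 = 0.59.

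**The case against.** The strongest reply is that the loss depends on choices the protocol leaves open. Nothing ends the trend analysis at week 34, and follow-up to an assumed week 40 gives six visits common to all. A gestational-age window starting at week 30 excludes nobody because of her entry date. A window of 4 or 5 visits is a reasonable compromise. A statistical analysis plan, not at hand here, could fix the window. The primary 2HPG difference is a comparison of means, for which a t-test is named.

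Much of this stands as a limit on size. A reader might infer that most of the data or most of the women would be lost. The documents do not support that as a general statement: under uniform entry, windows of 3, 4 or 5 visits keep most of both. Most women are lost only if 7 or 8 visits are required, and about half or slightly more at 6. The protocol requires no such number. Assumed missed visits could push the loss higher: at 10% missed, a five-visit window would keep 0.59 × 61-67%, or about 36-39% of women. But that rate is not in the documents. The protocol's 10% allowance is for non-respondents and is not a visit-level rate.

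The reply does not make the method fit. The protocol itself names the ANOVA, and an analysis plan that kept it could only choose what to discard. Lack of a named correction for sphericity is not part of this point, since standard corrections exist.

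**Conclusion.** The point holds as a mismatch between the named method and the protocol's own visit schedule. With entry assumed uniform and week 34 as the end point, the price is about 40-45% of measurements with three visits. With 4 or 5 visits it is about 17-40% of women and 36-40% of measurements, and with all eight it is over 80% of women. At an assumed week 40 it is about 25-29% of measurements. These figures precede missed visits and early deliveries, for which the protocol gives no rates. The 3-to-8 count rests on the protocol alone; every percentage rests on an assumed entry distribution.

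Two wider conclusions might be drawn and should not be. First, the t-test on 2HPG and the 47 per group are not affected. Second, a better trend model does not by itself bring every randomised woman into the comparison. The Metformin Group section removes women given supplemental insulin from that group, which is a separate matter.

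**What to change.** In Statistical Analysis, replace the repeated measures ANOVA for the trend comparison with a linear mixed model for repeated measures, and specify:

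- fixed effects for treatment, time, treatment-by-time and the baseline value of the glucose measure being analysed;
- whether time is gestational age or weeks since entry;
- a within-woman covariance structure;
- use of all available post-baseline values, with no requirement for a complete set;
- the between-group difference reported with its 95% CI.

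SPSS 20, already named, fits this with its MIXED procedure. The cost is one sentence in the protocol and slightly more analysis work. Visits, sample size and the t-test stay as they are.
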